### Randomization and blinding

Patients will be randomly allocated to one of the two conditions: MBI and active control group. Patients will be randomized to the intervention or control group with a 1:1 ratio, using a block-wise randomization sequence (block size of 4 and 6).

The sequence will be determined by an independent researcher, blind to initial assessment to ensure allocation concealment, using a random number generator (www.randomizer.org).

Treatment assignment will be communicated to the patients by the study coordinator to ensure the blinding of the evaluators.

One family member or caregiver for each patient is asked to join the group the patient has been assigned to. Because it is not possible to stratify for this variable, and as it is not our primary outcome, we expect that due to randomization the proportion of caregivers participating in the study will be distributed randomly and equally in both groups.

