#### Mindfulness based intervention (MBI)

The MBI is based on Mindfulness Based Stress Reduction (MBSR) [42] and Mindfulness Based Cognitive Therapy (MBCT [43] protocols. The MBI comprises an 8-week group program. Participants will took part in a 3 h single weekly sessions, and there will be also an additional all-day session of 7 h. Each session will cover specific exercises and topics within the context of mindfulness practice and training (body scan, breath meditation, walking meditation, yoga exercises). Participants will be required to carry out daily 45-min homework assignments, which consist on mindfulness exercises and mindfulness applications in everyday life. We will attempt to objectively verify the execution of homework practice through the clinical diary.

In order to maximize the clinical utility in people with MS suffering from depressive symptoms, we will tailor mindfulness intervention on the needs of this specific population [44].

We will apply a modified MBSR protocol integrated with techniques from Sensorimotor Psychotherapy (SP) [45], in which:particular emphasis will be paid to somatic resources (grounding, centering, boundaries, lengthening the spine, body self-soothing techniques, etc.) to stabilize the emotional state to prepare and sustain the mindful disposition;explanation of stress response will be integrated with the concept of “window of tolerance” [46], that is the range of optimal arousal which is necessary to stay in touch with the present moment experience. This concept allows a more precise awareness of the arousal state, recognizing hyper-arousal and hypo-arousal symptoms, and consequently to manage them more effectively;considering the attention deficits, which may be due both to neuropsychological deficits and to the depression itself, great attention is paid to attention training;considering interpersonal deficits in depression, interpersonal mindful listening is specifically addressed, developing the capacity to listen in a mindful state, creating a space inside to observe in a compassionate and non-judgmental way sensations, emotions and thoughts evoked by the other’s narration;great treatment emphasis will be paid on acceptance and self-compassion, and specific tools are used to increase it, such assessment and decentering of negative cognitions, and mindful body self- touch, becoming aware of sensations, feelings, thoughts and needs in the intimate relationship with the self.

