#### Outcome measures and statistical analysis

Primary outcome measures will be: 1) the improvements of BDI-II score from T0 to T2; 2) the proportion of participants at T2 that do not have a BDI-II score greater than 13.

Secondary outcome measures will be the comparison of the scores of FAMS, BAI, FSS, IIP, IPQ-Brief, PSS, PTGI and FFMQ of the two groups at T0, T1 and T2. Another secondary outcome aim will be the reduction of psychological symptoms (BDI-II, BAI, IIP, PSS, PTGI) and a reduction in QoL (WHOQoL-Brief) in caregivers of patients with MS.

The efficacy of MBI will be evaluated by comparing the results to different instruments administered to patients before participating at MBI (T0), after MBI (T1) and at the 6-month follow-up (T2) and by comparing these results with those of patients who were included in the active control group. Intention to treat analyses will be used.

A longitudinal (within subjects) and cross sectional (between subjects) evaluation of our outcome measures will be performed through a repeated measures multivariate analysis of covariance (ANCOVA) using the SPSS GLM procedure. The pre-treatment value will be the covariate, and the treatment condition will be the inter-subjects factor. The intra-subject factor will be a time condition, relating to changes from post-treatment to 6-month follow-up.

The proportion of participants at T1 and T2 no longer meeting the BDI-II cut-off criteria for depression will be evaluated through the Chi square test.

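### Randomisation does not secure equal caregiver participation if caregivers decide once the arm is known, and the caregiver outcome puts two scales in the wrong direction

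*Protocol article*

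**What the plan says.** In the protocol article, Randomization and blinding, only patients are randomised: "Patients will be randomized to the intervention or control group with a 1:1 ratio, using a block-wise randomization sequence (block size of 4 and 6". Patients learn their arm: "Treatment assignment will be communicated to the patients by the study coordinator to ensure the blinding of the evaluators". On caregivers the section says: "One family member or caregiver for each patient is asked to join the group the patient has been assigned to". It continues "Because it is not possible to stratify for this variable", notes that caregiver participation is not the primary outcome, and concludes that "we expect that due to randomization the proportion of caregivers participating in the study will be distributed randomly and equally in both groups".

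The Background lists efficacy of MBI on caregivers' depression, QoL and related symptoms among the secondary aims, and expects caregivers to gain from taking part. The Discussion repeats that expectation and counts caregiver involvement among the trial's main strengths.

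Under Outcome measures and statistical analysis, the caregiver outcome is "the reduction of psychological symptoms (BDI-II, BAI, IIP, PSS, PTGI", followed by "and a reduction in QoL (WHOQoL-Brief) in caregivers of patients with MS".

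**The concern.** There are two separate matters.

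**Balance.** Random allocation of patients balances, in expectation, what exists before allocation, such as whether a patient has a caregiver who could attend. If the caregiver agrees or declines after the arm is known, participation can be a consequence of the arm. Randomisation then gives no assurance that the proportions match, or that the same kinds of caregiver join each arm. A stated secondary aim would rest on a comparison of self-selected subsets. The promise of intention-to-treat analysis does not repair this, because a caregiver who declined after hearing the arm was never enrolled and has no data.

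**Direction.** The sentence defining the caregiver outcome states as its aim a fall in quality of life and a fall in a scale of positive change. Both run against the protocol's own expectation of benefit.

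**Working it through.** The protocol states no figure for caregiver participation, so there is none to reproduce. The check is one of logic, with illustrations whose uptake rates are assumptions.

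**1. Order of events.** The text has the patient allocated, the patient told, and the caregiver asked to join the group already assigned. It also says stratification cannot be done. That fits participation being unknown at randomisation, since a status known beforehand could serve as a stratum. The protocol gives no reason of its own, so this is an inference.

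**2. Does anything differ by arm that could move uptake?** Both arms have 8 weekly sessions of 3 h. MBI alone adds a long day ("there will be also an additional all-day session of 7 h").
- MBI: 8 × 3 + 7 = 31 h.
- Control: 8 × 3 = 24 h.

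Both arms are given homework. It is firmer in MBI and left to encouragement in control, which is a difference of degree. The 7 h session is the clear difference in burden.

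**3. Best case: the same uptake probability p in both arms, 44 patients per arm.** The SD of the between-arm difference in proportions is √(2p(1−p)/44).
- p = 0.30 or 0.70: √(0.42/44) = 0.098, or 9.8 points.
- p = 0.50: √(0.50/44) = 0.107, or 10.7 points.

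Exact binomial calculation over p = 0.30, 0.50 and 0.70 gives a 29–34% chance of a gap of at least 10 points and a 5–7% chance of at least 20 points. Even here, equality holds only on average.

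**4. Uptake that depends on the arm.** The expected gap is then no longer zero. Illustrations only:

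| Assumed uptake, one arm vs the other | Expected caregivers of 44 | Gap |
|---|---|---|
| 60% vs 50% | 26.4 vs 22.0 | 4.4 |
| 70% vs 50% | 30.8 vs 22.0 | 8.8 |
| 70% vs 40% | 30.8 vs 17.6 | 13.2 |

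Nothing in the protocol supports any particular row.

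**5. Caregiver status recorded before allocation.** With 26, 44 or 62 of 88 patients having a participating caregiver and an exact 44/44 split, the hypergeometric SD of the gap is 9.8, 10.7 and 9.8 points. The chance of a gap of at least 20 points is about 3–5%. Chance imbalance is therefore much as in step 3. What changes is that any gap is due to chance alone and the caregivers in the two arms are comparable in expectation. The converse matters too: equal numbers observed under the present wording would not show that the two sets of caregivers are alike.

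**6. Direction of the caregiver scales.** Six are listed: BDI-II, BAI, IIP, PSS, PTGI and WHOQoL-Brief.
- *QoL*: the outcome section speaks of a reduction; the Background and Discussion expect benefit. These conflict.
- *PTGI*: the outcome section places it among symptoms to be reduced; the Assessments section describes it as an instrument for positive outcomes. These conflict.
- *BDI-II, BAI, IIP, PSS*: a reduction is the beneficial direction.

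Two of six are reversed.

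**The case against.** The strongest reply is that the timing is inferred. The text fixes which group a caregiver attends, not when the caregiver is identified, consents or completes T0. A caregiver recruited alongside the patient, who then follows the patient's arm, would fit the same words, and a journal article may leave that sequence to the full protocol. This stands as a limit on certainty. It does not rescue the text, because if participation is known before allocation, the statement that stratification cannot be done is left unexplained.

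A reader might go further and infer that unequal caregiver attendance confounds the primary BDI-II comparison. The documents do not support that. Patients are randomised 1:1 and analysed by intention to treat. Attendance that arises after allocation is part of what assignment brings about, so the effect of assignment stays unbiased. What remains is interpretive: the Discussion wants the active control to isolate the role of mindfulness training, and unequal caregiver presence would be a second difference between arms.

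A reader might also infer that uptake will in fact differ, or that the arms differ widely in appeal. Neither is shown. Both programmes are active, weekly and led by a psychotherapist, and the control section names the missing all-day session as the sole departure in format.

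Lastly, one might conclude that the trial would score worse caregiver QoL as success. Taken alone the sentence says so, but nothing in the planned covariance analysis does, and the benefit expected elsewhere makes a drafting slip likely. The Background does not mention PTGI, so the case on that scale rests on the Assessments section alone.

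**Conclusion.** The concern holds in a limited form. The claim that randomisation will equalise caregiver participation does not follow if caregivers decide with the arm known. That is the natural reading and fits the remark about stratification, but it is not explicit. On that reading, the caregiver comparison, a secondary aim, is open to selection bias of unknown size. The protocol gives no uptake rate, and the figures for uptake above are assumptions. The primary patient comparison is not biased by this; at most, attributing its effect to mindfulness becomes harder.

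The direction error depends on no assumption about timing. The caregiver outcome as worded contradicts the protocol's own text on two of six scales.

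**What to change.** - Before allocation is disclosed, record for each patient whether a caregiver will take part, obtain the caregiver's consent and collect the T0 questionnaires.
- Analyse every caregiver enrolled in this way in the patient's assigned arm, whatever the later attendance.
- Optionally, use the pre-allocation yes/no indicator as a covariate or as a stratum for the block randomisation. Do not adjust for attendance after allocation, since it may be a result of the arm.
- If this sequence is not adopted, delete the statement that participation will be equal and describe the caregiver comparison as one between self-selected participants. If it is already the practice, say so and revise the remark on stratification.
- Reword the caregiver outcome as an improvement in QoL (WHOQoL-Brief), and move PTGI out of the symptoms to be reduced, stating that benefit is an increase.

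The cost is a reordering of consent steps and a short wait for the caregiver's answer before randomisation, plus a second block list if the stratum is used. The outcome correction is an edit to one sentence.

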### Assessments

All patients in the care of the CReSM are evaluated by neurologists with the EDSS (Expanded Disability Status Scale). The psychological assessment will be performed with the same timing and tools: at baseline (T0), after treatment (T1) and 6 months after the end of the group intervention (T2). The psychological assessment of the patients entering the study will be performed by trained Clinical Psychologists with more than 3 years of clinical practice in the liaison setting. The psychological assessment will be independent and blind to treatment, and will encompass the administration of the following clinical interview and self-report questionnaires.Structured Clinical Interview-DSM-IV (SCID-IV) [31]: is a well-validated, semi-structured interview, which covers the Diagnostic and Statistical Manual of Mental Disorders, 4th Edition (DSM-IV) criteria for adult psychopathology.Beck Depression Inventory-II (BDI) [32]: it is a 21-item self-report instrument that assesses the presence and severity of symptoms consistent with the criteria of the DSM-IV. Each item is scored on a 4 point scale ranging from 0 to 3 with total scores ranging from 0 to 63, where higher scores are indicative of higher levels of depression. The Consensus Group for depression in MS [12] and the American Academy of Neurology [13] stated that the best approach to screening for depression in general MS populations is to use the BDI-II, with a cut-off score of 13.Functional Assessment of Multiple Sclerosis (FAMS) [33]: it is a self-report scale designed to assess six primary aspects of QOL of patients with MS: Mobility, Symptoms, Emotional Well-Being, General Contentment Thinking and Fatigue, and Family/Social Well-Being.Beck Anxiety Inventory (BAI) [34]: is a 21-item self-report measure that assesses cognitive, somatic, and affective anxiety symptom severity. Each item is rated on a Likert scale from 0 to 3, and the total BAI score can range from 0 to 63, where higher scores are indicative of higher levels of anxiety.Fatigue Severity Scale (FSS) [35]: is a self-administered questionnaire with 9 items investigating the severity of fatigue in different situations during the past week. This items are designed to differentiate fatigue from clinical depression.Inventory of Interpersonal Problems (IIP) [36]: is a self-report instrument that identifies a person’s most salient interpersonal difficulties. The IIP contains 64 statements describing common interpersonal problems.Brief Illness Perception Questionnaire (IPQ-Brief) [37]. It is a nine item self-report measure that is used to assess the major components of illness perceptions. The questionnaire assesses each dimension using a single-item scale from 0 to 10.Perceived Stress Scale (PSS) [38]. It is a 10-item measure of the degree to which situations in one’s life are appraised as stressful. The items refer to people’s subjective appraisals of events.Post Traumatic Growth Inventory (PTGI) [39], a 21-item instrument for assessing positive outcomes in people who have experienced traumatic events. It measures five domains or factors: relating to others, new possibilities, personal strength, spiritual change, and a deeper appreciation of life.Five Facet Mindfulness Questionnaire (FFMQ) [40], a 39-item self-report questionnaire measuring five unique facets associated with the overarching construct of mindfulness disposition. The facets included are observing, describing, acting with awareness, nonjudgment, and nonreactivity.A clinical diary of the homework practice: it is a clinical diary regarding frequency and duration of homework assigned in the group sessions, that patients are asked to fill out every time they spent time on homework practice.

Caregivers will be asked to complete the same self-report measures administered to the patients, except for the FSS and the IPQ-Brief, which are related to the disease. Instead of FAMS, caregivers will complete the WHO-Quality of Life Brief [41].

### Intervention

Treatments will be independent and blinded from the clinical psychologists conducting the clinical assessments. The experimental group will undergo a 8 weekly sessions of 3 h each with a group based Mindfulness Based Intervention. The control group will follow the same structure as the Mindfulness Based Intervention.

#### Mindfulness based intervention (MBI)

The MBI is based on Mindfulness Based Stress Reduction (MBSR) [42] and Mindfulness Based Cognitive Therapy (MBCT [43] protocols. The MBI comprises an 8-week group program. Participants will took part in a 3 h single weekly sessions, and there will be also an additional all-day session of 7 h. Each session will cover specific exercises and topics within the context of mindfulness practice and training (body scan, breath meditation, walking meditation, yoga exercises). Participants will be required to carry out daily 45-min homework assignments, which consist on mindfulness exercises and mindfulness applications in everyday life. We will attempt to objectively verify the execution of homework practice through the clinical diary.

In order to maximize the clinical utility in people with MS suffering from depressive symptoms, we will tailor mindfulness intervention on the needs of this specific population [44].

We will apply a modified MBSR protocol integrated with techniques from Sensorimotor Psychotherapy (SP) [45], in which:particular emphasis will be paid to somatic resources (grounding, centering, boundaries, lengthening the spine, body self-soothing techniques, etc.) to stabilize the emotional state to prepare and sustain the mindful disposition;explanation of stress response will be integrated with the concept of “window of tolerance” [46], that is the range of optimal arousal which is necessary to stay in touch with the present moment experience. This concept allows a more precise awareness of the arousal state, recognizing hyper-arousal and hypo-arousal symptoms, and consequently to manage them more effectively;considering the attention deficits, which may be due both to neuropsychological deficits and to the depression itself, great attention is paid to attention training;considering interpersonal deficits in depression, interpersonal mindful listening is specifically addressed, developing the capacity to listen in a mindful state, creating a space inside to observe in a compassionate and non-judgmental way sensations, emotions and thoughts evoked by the other’s narration;great treatment emphasis will be paid on acceptance and self-compassion, and specific tools are used to increase it, such assessment and decentering of negative cognitions, and mindful body self- touch, becoming aware of sensations, feelings, thoughts and needs in the intimate relationship with the self.

MBI groups will be delivered by a psychotherapist with mindfulness training experience, who is experienced in working with people with MS.

#### Active control group

Our control group is based on the active control group of the study of Grossman et al. [47].

This intervention was designed to control for the non-specific elements of the MBI treatment. It will be based on a psycho-educational framework and will include some relaxation techniques.

In each session is discussed a MS-related topic. Relaxation and gentle stretching exercises will be proposed at the end of each session. Homework and the material (photocopies, slides, etc.) discussed in group sessions is left to each participant to encourage participants to practice exercises between sessions. This intervention will follow the same structure and weekly format of the MBI intervention. The only difference will be the absence of an all-day session. Each component has its counterpart in the MBI curriculum, but emphasis is placed upon not describing or training mindfulness skills to the control group. The groups will be delivered by a psychotherapist with relaxation training experience, who is experienced in working with people with MS.

#### Outcome measures and statistical analysis

Primary outcome measures will be: 1) the improvements of BDI-II score from T0 to T2; 2) the proportion of participants at T2 that do not have a BDI-II score greater than 13.

Secondary outcome measures will be the comparison of the scores of FAMS, BAI, FSS, IIP, IPQ-Brief, PSS, PTGI and FFMQ of the two groups at T0, T1 and T2. Another secondary outcome aim will be the reduction of psychological symptoms (BDI-II, BAI, IIP, PSS, PTGI) and a reduction in QoL (WHOQoL-Brief) in caregivers of patients with MS.

The efficacy of MBI will be evaluated by comparing the results to different instruments administered to patients before participating at MBI (T0), after MBI (T1) and at the 6-month follow-up (T2) and by comparing these results with those of patients who were included in the active control group. Intention to treat analyses will be used.

A longitudinal (within subjects) and cross sectional (between subjects) evaluation of our outcome measures will be performed through a repeated measures multivariate analysis of covariance (ANCOVA) using the SPSS GLM procedure. The pre-treatment value will be the covariate, and the treatment condition will be the inter-subjects factor. The intra-subject factor will be a time condition, relating to changes from post-treatment to 6-month follow-up.

The proportion of participants at T1 and T2 no longer meeting the BDI-II cut-off criteria for depression will be evaluated through the Chi square test.

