**Methods:**

The study design is a randomized controlled clinical trial. Eighty-eight patients with Multiple Sclerosis and depressive symptoms will be recruited and randomized to either Mindfulness Based Intervention or an active control group. The latter is designed to control for non-specific elements of the intervention and it comprises psycho-education and relaxation techniques. The primary outcome is the reduction of depressive symptoms as measured via the Beck Depressive Inventory-II. Secondary outcome measures are level of quality of life, anxiety, perceived stress, illness perception, fatigue and quality of interpersonal relationship. Outcomes will be assessed at baseline, after treatment and 6 months after the end of the treatment. Caregivers will participate in groups together with patients.

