#### Power calculation

The sample size calculation is based on the primary outcomes for patients with MS.

Statistical power calculation was based on previous studies [28, 48]: assuming power =0.80 and 0.05 significance, a minimal sample size of 44 patients/group will be required, based on an effect size of 0.54.

To obtain the 88 patients needed for the study, it is expected to do the screening of at least 600 patients. On the basis of the information that is available on the prevalence of depression in MS patients, on the average 25 % in previous studies, this number should guarantee there will be at least 150 participants. The number of refusals and treatment interruptions is estimated at not above 40 % which leads to about 90 cases.

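### Two primary outcomes from the same T2 BDI-II score have no rule linking them, and the one sample size claimed for both does not give 80% power for the proportion

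*Protocol article*

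**What the plan says.** Three places in the protocol article bear on what decides success.

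- The Methods part of the abstract is in the singular: "The primary outcome is the reduction of depressive symptoms as measured via the Beck Depressive Inventory-II".
- Outcome measures and statistical analysis lists two: "Primary outcome measures will be: 1) the improvements of BDI-II score from T0 to T2", followed by "2) the proportion of participants at T2 that do not have a BDI-II score greater than 13". The score goes into a repeated-measures ANCOVA, for which "The pre-treatment value will be the covariate, and the treatment condition will be the inter-subjects factor". For the other outcome, "The proportion of participants at T1 and T2 no longer meeting the BDI-II cut-off criteria for depression will be evaluated through the Chi square test". The section gives no significance level, no order of testing, and no statement of whether one or both results must be significant.
- Power calculation opens with "The sample size calculation is based on the primary outcomes for patients with MS" and continues "assuming power =0.80 and 0.05 significance, a minimal sample size of 44 patients/group will be required", with an effect size of 0.54. It does not say what kind of effect size this is or whether the test is one- or two-sided. It gives no proportion and no difference in proportions.

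The cut-off in the second outcome is also the entry threshold (Participants).

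**The concern.** Both outcomes rest on the same T2 score. Once baseline is a covariate, testing the improvement is the same as testing the T2 score, and the second outcome is that score cut at 13. Two primary tests without a linking rule leave open which result makes the trial positive. If either will do, two chances at 0.05 push the false-positive rate above 5%. If both are needed, the trial is only as strong as its weaker test, and a cut score carries less information than the score itself. The power statement claims cover for both outcomes, so a reader would assume that the proportion also has 80% power at 44 per group. A clear result on one outcome and a null result on the other is therefore quite likely, and the article gives no way to read it.

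**Working it through.** **Inputs from the article:** 44 per group, 1:1 allocation, significance 0.05, power 0.80, effect size 0.54, cut-off 13.

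**Assumptions, because the article gives no figure:** 0.54 is a standardised mean difference; the control proportion at or below 13 at T2 lies between 0.20 and 0.70; the T2 score is normal; the baseline-to-T2 correlation lies between 0 and 0.7.

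**1. The plan's own figure.** For two means, n per group = 2(z_α + z_β)² / d².

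- Two-sided 0.05: 2(1.960 + 0.842)² / 0.54² = 53.8, so 54 (exact t: 55). This is not 44.
- One-sided 0.05: 2(1.645 + 0.842)² / 0.54² = 42.4, so 43 (exact t: 43.1, rounded up to 44). This reproduces the plan.
- Two-sided with baseline adjustment: n shrinks by (1 − r²), so 44 needs r = √(1 − 44/54) = 0.43. No correlation is stated.
- Two-sided unadjusted power at 44: Φ(0.54·√22 − 1.960) = Φ(0.573) = 0.72 (exact t: 0.71).

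So 44 is what one comparison of means gives, on one of two unstated bases.

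**2. The proportion, at the same effect.** A shift of 0.54 SD turns a control proportion p_C into p_T = Φ(Φ⁻¹(p_C) + 0.54). For p_C = 0.40, p_T = Φ(−0.253 + 0.54) = 0.613. Power = Φ[(|p_T − p_C| − z_α·SE₀) / SE₁], where SE₀ is the pooled and SE₁ the unpooled standard error. Here SE₀ = √(0.506 × 0.494 × 2/44) = 0.1066 and SE₁ = √((0.400 × 0.600 + 0.613 × 0.387)/44) = 0.1042. Two-sided power is Φ[(0.2128 − 1.960 × 0.1066)/0.1042] = 0.515.

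| Control ≤13 | MBI ≤13 | Power, two-sided | Power, one-sided | n per group for 80%, two-sided | n per group for 80%, one-sided |
|---|---|---|---|---|---|
| 0.20 | 0.381 | 0.465 | 0.593 | 98 | 77 |
| 0.30 | 0.506 | 0.505 | 0.631 | 88 | 69 |
| 0.40 | 0.613 | 0.515 | 0.641 | 86 | 68 |
| 0.50 | 0.705 | 0.504 | 0.630 | 88 | 70 |
| 0.60 | 0.786 | 0.473 | 0.600 | 96 | 75 |
| 0.70 | 0.856 | 0.422 | 0.549 | 110 | 87 |

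With 44 per group and 40% in the control group, 80% power needs about 69% in the MBI group two-sided, or 66% one-sided, against the 61% that a 0.54 SD shift gives.

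**3. Either outcome counts.** Two independent tests would give 1 − 0.95² = 9.75%. The tests share a score, so the rate is lower. Simulating the T2 ANCOVA and the uncorrected chi-square with no treatment effect (44 per group, two-sided 0.05) gives 7.4% to 9.2% for control proportions of 0.3 to 0.6. Over all the assumptions above, about 7 to 10% is a fair summary.

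**4. Both outcomes needed.** The joint error is only 1.0% to 2.2%. Joint two-sided power for a 0.54 SD shift is 0.47 to 0.49 at control proportions of 0.30 to 0.50 and falls to about 0.40 at 0.70. It can never exceed the power of the chi-square alone, so it stays below about 0.52 two-sided and 0.64 one-sided.

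**5. Splitting the level.** At 0.025 two-sided for each outcome, simulated either-outcome error is 4.0% to 4.7%. The unadjusted score then has power of about 0.60 to 0.61 at 44 per group and needs 66 per group for 80%. The proportion has power of 0.31 to 0.40.

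**The case against.** **Details left to a fuller document.** An article may leave testing order and alpha handling to an analysis plan that is not shown. That stands for the missing rule taken alone. It does not cover the number of primary outcomes or the claim about what the sample size covers, both of which the article states.

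**The abstract.** Its sentence names a construct and an instrument, and both listed outcomes could fall under it. So it is a looser description and not a flat contradiction, but it does not settle which outcome decides.

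**The kind of effect size.** If 0.54 were Cohen's h for two proportions, the formula in step 1 applies to the proportion, which would then have about 80% power one-sided (about 0.72 two-sided), and the score would have more. That would weaken the power argument. Nothing in the article says so, however. A 0.54 SD shift corresponds to an h of only about 0.41 to 0.43, so one value of 0.54 cannot describe both outcomes, and the either-outcome error would remain.

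**Stronger readings that the article does not support.**

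- A reader might infer that the false-positive rate exceeds 5% outright. It does so only if either result counts, and no section says that.
- A reader might infer that each test is declared at 0.05. That level appears only in the power calculation; applying it to each test is an inference.
- A reader might add the T1 chi-square and quote a higher error rate. The second primary outcome is defined at T2 only, so the T1 test is not a primary test.
- A reader might call the unadjusted chi-square wrong because it ignores baseline. It is valid under randomisation; adjustment would only gain efficiency.
- A reader might object to the cut-off itself. It is the entry threshold, is given consensus support in the article, and sits beside the continuous score.

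**Conclusion.** The point holds. The article names two primary outcomes on one score, gives no rule joining them, and claims one sample size for both. With 0.54 as a standardised mean difference, neither success rule delivers 5% error together with 80% power for both outcomes: about 7 to 10% false positives if either counts, or about 0.40 to 0.49 joint two-sided power if both are needed. The power for the proportion depends on control proportions that the article does not give, but it is below 0.80 across the whole assumed range of 0.20 to 0.70, one- or two-sided. The claim for the score is sound only on an unstated basis: a one-sided test, or a baseline correlation of about 0.43. Otherwise its two-sided power is about 0.71. This should be corrected before analysis; it does not invalidate the design.

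**What to change.** - Name baseline-adjusted BDI-II at T2 as the single primary outcome. This fits the abstract and the single effect size.
- Make BDI-II not above 13 at T2 the first secondary outcome, tested at the same level only if the primary result is significant. Present the T1 proportions as supportive. Adjusting the binary analysis for baseline BDI-II is an optional gain in efficiency.
- Reword Power calculation so that the 80% covers only the continuous outcome. State the kind of effect size, the sidedness and any baseline correlation assumed. If the test is two-sided and no correlation can be justified, state the power as about 0.71.

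This changes wording only, with no added patients or visits. The cost is that the sponsor can no longer claim success on the proportion alone. Keeping both as primary outcomes with a split level is possible, but at 44 per group it lowers unadjusted power for the score to about 0.61.
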